# The clinical effectiveness and cost-effectiveness of a ‘stepping into day treatment’ approach versus inpatient treatment as usual for anorexia nervosa in adult specialist eating disorder services (DAISIES trial): a study protocol of a randomised controlled multi-centre open-label parallel group non-inferiority trial

**DOI:** 10.1186/s13063-022-06386-7

**Published:** 2022-06-16

**Keywords:** Anorexia nervosa, Inpatient treatment, Day patient treatment, Partial hospitalisation, Intensive treatment, Stepped care

## Abstract

**Background:**

Anorexia nervosa (AN) is a serious and disabling mental disorder with a high disease burden. In a proportion of cases, intensive hospital-based treatments, i.e. inpatient or day patient treatment, are required, with day patient treatment often being used as a ‘step-down’ treatment after a period of inpatient treatment. Demand for such treatment approaches has seen a sharp rise. Despite this, the relative merits of these approaches for patients, their families, and the NHS and wider society are relatively unknown. This paper describes the rationale for, and protocol of, a two-arm multi-centre open-label parallel group non-inferiority randomised controlled trial, evaluating the effectiveness and cost-effectiveness of these two intensive treatments for adults with severe AN: inpatient treatment as usual and a stepped care day patient approach (the combination of day patient treatment with the option of initial inpatient treatment for medical stabilisation). The main aim of this trial is to establish whether, in adults with severe AN, a stepped care day patient approach is non-inferior to inpatient treatment as usual in relation to improving body mass index (BMI) at 12 months post-randomisation.

**Methods:**

386 patients with a Diagnostic and Statistical Manual 5th edition diagnosis of severe AN or related disorder, with a BMI of ≤16 kg/m^2^ and in need of intensive treatment will be randomly allocated to either inpatient treatment as usual or a stepped care day patient approach. Patients in both groups will receive treatment until they reach a healthy weight or get as close to this point as possible. Assessments will be conducted at baseline (prior to randomisation), and at 6 and 12 months post-randomisation, with additional monthly symptom monitoring. The primary outcome will be BMI at the 12-month post-randomisation assessment. Other outcomes will include psychosocial adjustment; treatment motivation, expectations and experiences; cost-effectiveness; and carer burden.

**Discussion:**

The results of this study will provide a rigorous evaluation of two intensive treatment approaches which will inform future national and international treatment guidelines and service provision.

**Trial registration:**

ISRCTN ISRCTN10166784. Registered 28 February 2020. ISRCTN is a primary registry of the World Health Organization (WHO) International Clinical Trials Registry Platform (ICTRP) network and includes all items from the WHO Trial Registration Data Set.

## Background

Anorexia nervosa (AN) is a serious mental disorder associated with high levels of mortality and disability, physical and psychological morbidity, and impaired quality of life [1–3]. At a time when admission rates for most other major mental disorders (e.g. schizophrenia, depression, bipolar disorder and dementia) have fallen [4], hospital admission rates for AN have seen a sharp rise. For example, the Oxford Record Linkage Study reported that the age standardised first-recorded admission rate for women (aged 10–44 years) has increased from 2.7 per 100,000 of the female population in 1968–1971 to 6.3 in 2007–2011 and for males, 0 per 100,000 in the 1960s to 0.4 per 100,000 in 2007–2011 [5]. Country-wide data have shown a similar trend [5]. More recently, NHS Digital data have revealed that admissions for eating disorders (EDs) have risen 37% across all age groups over a 2-year period from 2016/17 and 2018/19 [6]. A potential alternative to inpatient treatment for severely unwell patients with AN is day treatment. Often this is used as a step-down treatment after an initial period of inpatient treatment for medical stabilisation [7–9]. However, the relative merits of these two intensive treatment approaches for patients with severe AN, their families, and the NHS and wider society are relatively unknown. Therefore, this study aims to compare the clinical and cost-effectiveness of inpatient treatment as usual (IP-TAU), the current standard care pathway, to a stepped care day treatment approach, which combines intensive day patient treatment with the option for initial inpatient treatment for medical stabilisation and progression to day patient treatment at the earliest opportunity, for adults with severe AN.

Both of these intensive treatment approaches have potential risks and benefits for both the patient and their carers. IP-TAU is widely considered the gold standard for patients with severe AN, as it offers intensive support around feeding and safety monitoring. It may also give families a much-needed respite from looking after their relative. Patients may feel that they are part of a ready-made community of people with similar problems. However, especially if the admission is prolonged, as is common, it may lead to patients becoming institutionalised, passive and disempowered and make it harder for them to translate gains made whilst in hospital into their life in the community. In contrast, a stepped care day treatment approach allows for the delivery of flexible personalised care tailored according to patient risk and progress and for patients to retain better links with their family and friends. It may also help them realise that they need to be actively involved in their own recovery, and by doing so may make them more resilient against relapse and able to cope with any setbacks. Likewise, this approach may also help carers feel more empowered to support the person at home. However, having intensive support only for part of the week may make it harder to achieve substantial weight gain, necessary for recovery. Daily travel may pose practical challenges for patients living at a distance and having to spend evenings and weekends at home may increase feelings of loneliness and isolation. It may also increase burden on families. Ultimately, the risk and benefit ratio will vary from case to case and it is currently unknown whether treatment outcomes from these approaches are comparable.

In addition to patient-specific outcomes (i.e. weight and psychosocial outcomes), the impact on a system level, e.g. the cost-effectiveness of the two approaches, is also an important consideration. AN has one of the highest treatment costs of any psychiatric disorder [23–25]. This is largely due to the high cost of inpatient treatment, which is directly related to illness severity (i.e. body mass index [BMI]), as this affects length of stay [25]. Guarda et al. [26] reported that whilst, in the USA, the average cost per day was $2295 for inpatient treatment and $1567 for day treatment, the average cost per pound in weight gained was $4089 and $7050 respectively, suggesting that inpatient treatment may be a more efficient way of achieving weight recovery. However, this study only focused on cost related to short-term weight outcomes, and longer-term weight and psychological outcomes were not considered. In contrast, the previously described RCT by Herpertz-Dahlmann et al. [19] found that the stepped care day patient treatment approach (i.e. a short inpatient admission followed by day treatment) for adolescents with AN was less costly than inpatient treatment, and the previously described study by Zanna et al. [22] reported no significant difference in costs between inpatient and day patient treatment.

At present, it is unclear how a day patient treatment approach compares to inpatient treatment for an adult population with severe AN within the context of different health care systems. To gauge how inpatient and day treatments are used for adults with AN, we reviewed admission BMIs and length of stay in naturalistic studies of these treatments. For day treatments, based on a narrative review [9] and two further studies [7, 26], we identified 11 uncontrolled studies (*n* = 1010 AN patients) from different countries (USA, Canada, Australia, Germany, Italy, Holland, UK). Across these studies, admission BMIs ranged from 15.7 to 18.7 kg/m^2^. With the exception of one study [26], all others had a mixture of patients who were stepped down from inpatient treatment or admitted from the community. Length of stay ranged from 32 to 182 days, with most programmes offering treatment for 10–16 weeks, and a recent meta-analytic review found a mean length of stay of 86.3 days [13]. For inpatient treatment, 15 adult inpatient cohorts (*n* = 2100) from different countries (USA/Canada, Australia/New Zealand, Germany, Italy, UK) reported mean admission BMIs ranging from 13.9 to 16.3 kg/m^2^ [26–42] and a meta-analysis reported a mean length of stay of 105.6 days across Europe and 49.1 days across USA [13]. A recent audit from the Quality Network for Eating Disorders in the UK, which included data submitted from all adult inpatient eating disorder services in England (*n* = 30) and two in Scotland (out of four adult inpatient eating disorder services), reported the mean length of stay for inpatient treatment as 116 days [43]. Taken together, these data suggest that internationally there is considerable variation in the severity and length of stay across intensive settings for patients with AN and the optimal length of intensive treatments for AN is unknown. Furthermore, it can be concluded that, internationally, day treatment is typically used for patients that do not have severe AN (as defined by BMI). Given this, there is limited evidence for the use of day treatment for our target population of severe AN.

In summary, relatively little is known about the comparative effectiveness, cost and cost-effectiveness of a stepped care day patient approach to inpatient treatment as usual for treating severe AN. If at least a proportion of patients needing intensive treatment could be treated as day patients, or be stepped down into day treatment from initial inpatient treatment, this could have significant cost savings. The proposed trial (the DAISIES study) aims to compare these two intensive treatment approaches in a two-arm multi-centre open-label parallel group non-inferiority RCT in adults with severe AN or related disorders in the National Health Service (NHS) of the UK.

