#### Inclusion and exclusion criteria

Inclusion criteria are as follows: (1) adults aged 17 years or above; (2) DSM-5 [50] diagnosis of AN or ARFID; (3) BMI of equal to or less than 16.0 kg/m^2^; (4) in need of intensive treatment because of either rapid weight loss, and/or evidence of system/organ failure/medical instability and/or unsuccessful outpatient treatment, as defined by NHS England [51]; and (5) have mental capacity to give informed consent to participate in the study. Exclusion criteria are as follows: (1) individuals with insufficient knowledge of English to complete study assessments or understand treatment; (2) individuals with severe learning disabilities; (3) individuals with a severe medical or psychiatric (co)morbidity (e.g. psychosis, substance dependence) requiring treatment in its own right; and (4) those living too far away from day patient treatment (and where no alternative arrangements for regular attendance at day patient treatment can be made).

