#### Sample size

The sample size calculation is based on a one-sided non-inferiority test at 97.5% confidence. Previous studies suggested a standard deviation for within-group BMI at 12 months of 2.3 kg/m^2^ [19, 38]. Based on Herpertz-Dahlmann et al. [19], we defined our non-inferiority threshold as a 0.75 kg/m^2^ decrease in BMI for stepped care relative to IP-TAU. If there is truly no difference between stepped care and IP-TAU, then 198 participants per trial arm are needed to be 90% sure that the lower limit of a one-sided 97.5% confidence interval (or equivalent a 95% two-sided confidence interval) for the difference will be above the non-inferiority limit of −0.75. To account for the precision gain due to including baseline BMI in the modelling, we applied a deflation factor (0.78, based on a pre-post correlation of 0.47, [38]) to the estimated sample size [52]. We also inflated the requirement to account for 20% dropout at 12 months based on our previous studies [53, 54]. This gave a final sample size requirement of 193 per trial arm (*n* = 386 in total).

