### Randomisation

The generation and implementation of the randomisation sequence will be conducted independently from the trial team through an online system provided by King’s Clinical Trials Unit (KCTU). Randomisation will be done at the level of the individual and stratified for known prognostic variables of outcomes (previous inpatient treatment [yes/no], illness duration [≤ or > 3 years] and recruitment centre). Minimisation with a stochastic component will be used to balance these three prognostics variables across trial arms. After the baseline assessment is completed, participant ID and stratification details will be entered into the web-based KCTU system by a member of the research team. Participants will then be randomly allocated on a 1:1 ratio to either (a) IP-TAU or (b) a stepped care day patient approach. A designated unblinded researcher in the trial team will oversee randomisation. This includes receiving the randomisation outcome from the online system and informing the participant’s treating clinical team of the allocated treatment arm. It will be the responsibility of the participant’s treating clinical team to inform the participant of their allocated treatment.

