### Data analysis

A detailed statistical analysis plan will be developed by the trial statisticians whilst maintaining full blind and agreed with the research team and Data Monitoring and Ethics Committee before the end of the internal pilot. Briefly, all formal comparisons of the two care pathways will follow the intention-to-treat principle. For continuous clinical outcomes variables, such as BMI, linear mixed models will be fitted to the outcome measures at 6 and 12 months to estimate the trial arm differences. The fixed part of these models will contain the explanatory variables of interest (trial arm, time and an interaction term) and also baseline values of outcome variables and randomisation stratifiers, as these variables are known to explain variability in outcome. To account for correlation between the repeated measures at 6 and 12 months, a subject-varying random intercept will be included. For non-continuous outcomes, relevant generalised linear mixed models will be fitted. Results are valid under a missing at random (MAR) missing data generating mechanism that allows earlier outcome values to predict missingness of later ones. In the presence of missing data, should we find that the assumptions underlying the mixed modelling approach are not realistic, then an alternative, more flexible approach such as multiple imputation will be used instead.

To judge non-inferiority of the stepped care approach in terms of the primary outcome (BMI at 12 months), a two-sided 95% confidence interval of the trial arm difference in this clinical measure will be generated and this interval compared with the non-inferiority threshold (0.75 kg/m^2^ decrease in BMI). The threshold defines a region for the trial arm difference in BMI in which the stepped care day patient approach would be considered non-inferior to IP-TAU. To confirm the non-inferiority hypothesis, the whole 95% confidence interval would need to lie within this region. Supplementary subgroup analyses will estimate care pathway differences in treatment-completer populations (defined using the minimal and full treatment completion criteria described previously) to investigate the impact of any treatment non-completion on the non-inferiority assessment. In this context, methods from the causal inference field, e.g. inverse probability weighting, will be used to adjust for variables driving both treatment completion and primary BMI outcome [75]. No other subgroup analyses are planned.

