#### Economic evaluation

The economic evaluation will take the NHS/personal social services perspective preferred by the National Institute for Health and Care Excellence (NICE) and shown in previous AN studies to constitute over 90% of total societal costs. Service use data will be collected using the Adult Service Use Schedule (AD-SUS), designed for use in adult populations with mental health conditions [71, 72] and modified for AN on the basis of relevant literature and clinical expertise. The AD-SUS is used to assess the number and length of contacts with various health and social care services and professionals, plus prescribed medications, over a period of time appropriate for each individual study. The DAISIES AD-SUS will be used at baseline to collect use of services in the previous 6 months and at the 6- and 12-month follow-ups to collect use of services since the previous interview. In this way, the full period from baseline to the 12-month follow-up will be covered. The AD-SUS is commonly administered in interview format. However, to avoid unblinding the research assessors, use of hospital services (inpatient, day patient, outpatient and Accident & Emergency) will be reported by participants using a self-report version of the AD-SUS. All remaining service use (i.e. community services and prescribed medications) will be collected in interview. This is to improve recall accuracy, whilst ensuring that the researchers remain blinded. In addition, the collection of data on use of hospital services from clinical records at each site will be piloted at baseline and, if successful, implemented at each follow-up. The self-report data will be secondary to the clinical records data and will be used where clinical data cannot be provided. Nationally applicable unit costs will be applied to all services, including the inpatient and day patient-based interventions [76, 77]. To supplement these data, Hospital Episode Statistics (HES) from NHS Digital (for participants from England) and Information Services Division (ISD; for participants from Scotland) will also be requested and incorporated if data is received in a timely fashion.

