Cost-effectiveness will be explored at the 12-month follow-up in terms of QALYs measured using the EQ-5D-5L [70], with a sensitivity analysis using the primary clinical measure of outcome (BMI), given the limited evidence available for the validity of the EQ-5D-5L in ED populations. QALYs will be calculated by applying appropriate utility weights to health states [78] and using the total area under the curve approach with linear interpolation between assessment points [79].

Mean differences in costs and 95% confidence intervals will be obtained by nonparametric bootstrap regressions to account for the non-normal distribution often found in economic data. Cost-effectiveness analyses will be undertaken irrespective of whether non-inferiority is demonstrated, since exploration of the joint distribution of costs and effects is recommended to represent uncertainty [80] and to help interpret the economic results [81]. Incremental cost-effectiveness ratios (ICERs) will be calculated if higher costs and better outcomes are found in either the stepped care day patient approach or IP-TAU group. Uncertainty around cost-effectiveness estimates will be explored using cost-effectiveness planes and cost-effectiveness acceptability curves (CEACs) based on the net-benefit approach [82]. All economic analyses will be adjusted in line with the clinical approach (baseline values of the variables of interest and randomisation stratifiers). Missing economic cost and outcome data will be imputed using multiple imputation methods by using chained equations, under the assumption that these data were missing at random [83].

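### On its natural reading, the cost regression leaves out baseline BMI, which the protocol itself links to inpatient cost; adding it is a free gain in precision of unknown, probably modest, size

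*Protocol article*

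**What the plan says.** All of the following is in the Protocol article.

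- **Background:** treatment cost is high largely because of "the high cost of inpatient treatment, which is directly related to illness severity (i.e. body mass index [BMI]), as this affects length of stay".
- **Economic evaluation:** "All economic analyses will be adjusted in line with the clinical approach (baseline values of the variables of interest and randomisation stratifiers"). The variables meant are not listed.
- **Data analysis**, which defines the clinical approach referred to: the fixed part of each model holds the trial-arm and time terms and "also baseline values of outcome variables and randomisation stratifiers, as these variables are known to explain variability in outcome".
- **Randomisation:** the minimisation factors are "previous inpatient treatment [yes/no], illness duration [≤ or > 3 years] and recruitment centre". BMI is not among them.
- **Table 1 and Baseline assessment:** weight and height are measured in every participant before allocation.
- **Economic evaluation**, on the source of baseline cost: "The DAISIES AD-SUS will be used at baseline to collect use of services in the previous 6 months". The same section plans QALYs as the main effect measure, "with a sensitivity analysis using the primary clinical measure of outcome (BMI").

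**The concern.** The Data analysis section justifies its covariates by their known power to explain the outcome. By the Background's own account, BMI meets that test for inpatient cost. Yet if the economic models follow the clinical pattern, baseline BMI enters only where BMI is itself the outcome.

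Two features of the design make the link plausible within the trial. Both pathways aim for a healthy weight or as near to it as possible, so a lower entry BMI may mean longer treatment. BMI is also one of the decision-tool indicators that help decide whether a stepped-care patient is treated as an inpatient or a day patient.

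Baseline cost may be a weak stand-in for severity. It covers the preceding 6 months, and the Screening section expects most recruits to come from community or outpatient settings.

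At stake are the width of the interval for the cost difference, and how far a chance difference in entry BMI could move that difference and, with it, the cost-effectiveness plane and acceptability curves. In the BMI-based sensitivity analysis, the effect difference would be adjusted for baseline BMI while the cost difference paired with it would not.

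**Working it through.** **1. Which covariates the cost model holds.** Taken together, the Economic evaluation, Data analysis and Randomisation sections give, on the natural reading:

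- cost model: baseline cost, previous inpatient treatment, illness duration, centre;
- QALY model: baseline utility and the same three stratifiers;
- BMI as effect measure: baseline BMI and the same three stratifiers.

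**2. The plan's own figure.** The article gives no precision figure for costs. Its sample size, for the primary BMI outcome, supplies the number of patients. Inputs from the Sample size section: SD 2.3, margin 0.75, one-sided 2.5%, power 90%, true difference 0.

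- n per arm = 2 × 2.3² × (1.960 + 1.282)² / 0.75² = 197.6, so 198, as stated.
- Deflation: 1 − 0.47² = 0.779, stated as 0.78.
- Dropout: 198 × 0.78 / 0.80 = 193.05, stated as 193 per arm, 386 in total.

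The figure reproduces and is unaffected by this point. The 0.47 there relates baseline BMI to later BMI, so it cannot stand in for a correlation with cost.

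**3. Gain in precision.** Let r be the partial correlation of baseline BMI with 12-month cost, given baseline cost and the stratifiers. The documents do not give it, so 0.1 to 0.4 is an assumption. In large samples, adding BMI multiplies the variance of the cost difference by 1 − r², so the interval narrows by 1 − √(1 − r²). The equivalent number of extra patients is 386/(1 − r²) − 386.

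| r (assumed) | Variance cut | CI narrower by | Equivalent extra patients on 386 |
|---|---|---|---|
| 0.1 | 1% | 0.5% | 4 |
| 0.2 | 4% | 2.0% | 16 |
| 0.3 | 9% | 4.6% | 38 |
| 0.4 | 16% | 8.3% | 74 |

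**4. Conditional imbalance.** With 193 per arm, the standard error of the standardised baseline difference is √(2/193) = 0.102 SD, so about 5% of trials show an imbalance beyond 1.96 × 0.102 = 0.20 SD. An imbalance at that limit shifts the cost difference, without BMI in the model, by r × 0.20 SD:

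- r = 0.1: 0.02 SD;
- r = 0.3: 0.06 SD, or 0.06/0.102 = 0.59 standard errors;
- r = 0.4: 0.08 SD.

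The half-width of the interval is 1.96 × 0.102 = 0.20 SD. With 154 evaluable per arm (20% dropout), the standard error is 0.114, the half-width 0.223 SD, and the shift at r = 0.3 is 0.067 SD. The ratio to the standard error is the same.

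**The case against.** The strongest reply is that no sentence excludes baseline BMI. The economic covariates are described in general terms, and a condensed article may leave the full list to an analysis plan that is not shown. This stands as a limit: the omission is a reading, though the natural one, because the section refers explicitly to a clinical approach that is defined elsewhere. For the same reason, the mismatch in the BMI-based sensitivity analysis is likely but not certain; the phrase could be taken to cover cost and BMI jointly.

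The second reply is that the gain may be negligible. Eligibility requires a "BMI of equal to or less than 16.0 kg/m^2", and this truncation may weaken the correlation. Baseline cost, previous inpatient treatment and illness duration may already absorb part of the severity effect. The Background remark is qualitative, concerns inpatient cost, and does not say that the link holds within this BMI range or in the stepped-care arm. All of this stands, and is why the range starts at 0.1.

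A reader might also infer that the economic comparison is biased. It is not. Randomisation protects it, and the confidence interval already covers chance imbalance in any covariate left out. The 0.59 standard-error shift describes an uncommon realised imbalance at an assumed r, not a systematic error. Nor do the documents support calling the QALY model deficient: the Background ties BMI to inpatient cost and says nothing about utility.

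**Conclusion.** The point holds as an improvement, not as an error. On the natural reading, the cost regression omits a baseline variable that the protocol names as a driver of inpatient cost and that is available for everyone. The analysis as planned is valid. The benefit is a narrower interval and less sensitivity to a realised imbalance in entry BMI. Its size is unknown: 0.5% to 8% narrowing for assumed partial correlations of 0.1 to 0.4, and possibly at the low end. The primary non-inferiority conclusion is untouched.

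**What to change.** In the Economic evaluation section, or in the analysis plan that implements it:

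- state that the cost and net-benefit regressions include baseline BMI as a continuous covariate, in addition to the baseline value of the variable analysed and the three stratifiers;
- state that the BMI-based sensitivity analysis uses the same covariates for the cost difference and the effect difference.

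Baseline BMI may be added to the QALY model if a common covariate set is wanted, but nothing in the documents requires it.

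The cost is a sentence or two, best settled before allocation is revealed to the analysts. No new data or patients are needed, and one continuous covariate uses one degree of freedom.
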